**Figure 1 F1:**
[figure not shown]
**Flowchart of patients in the trial.** CT - computed tomography, NGT - nasogastric tube, NPO - nil per os, SBO - small bowel obstruction.

Inclusion criteria:

– All patients with clinical and computed tomography-diagnosed adhesive small bowel obstruction

– Obstruction is not relieved by conservative methods (nasogastric tube, nil per os) including Gastrografin® is not passed to colon within 8 hours (48-hour conservative treatment without Gastrografin® is allowed if Gastrografin® is contraindicated (e.g. allergy) or not available)

Exclusion criteria:

– Strong suspicion of strangulation or clinical peritonitis requiring an urgent operative intervention

– Previously confirmed or strongly suspected peritoneal carcinosis

– Previously confirmed wide diffuse adhesions of the abdominal cavity

– Previous open surgery for endometriosis

– Previous generalized peritonitis (not including local peritonitis such as appendicitis)

– Active abdominal malignancy or remission of less than 10 years’ duration

– Previous radiotherapy of the abdominal region

– Previous obesity surgery

– 3 or more earlier open abdominal operations (not including caesarean section(s))

– Suspicion of other cause for obstruction than adhesions in CT-scan

– Recent abdominal operation (within 30 days)

– Previous laparotomy for aorta or iliac vessels

– Crohn's disease

– Anesthesiological contraindication for laparoscopy

– No informed consent

– Age less than 18 years or over 95 years

– Pregnancy

– Patient living in institutionalized care (such as health centre ward), not including retirement homes

– A hospital stay of more than one week prior to surgical consultation

### Randomization procedure

Patients are randomly allocated (1:1) to either laparoscopic or open surgery. Randomization is done using block randomization with randomly varying block size (2–6) stratified by each study center. Cards with participants’ randomization number and randomization group are sealed within numbered envelopes. Randomization and sealing within envelopes is done at the main research center (Helsinki) and letters are sent to each participating center at the beginning of the trial. The envelope is opened only after patient fulfills inclusion criteria, none of the exclusion criteria are met, and patient has agreed to participate in the study and has given a written consent. Envelopes are opened in numerical order. Operation is scheduled after randomization.

### Intervention

#### Pre- and perioperative treatment

Fluid balance and electrolyte disturbancies are corrected. Prophylactic cefuroxime 1500 mg and metronidazole 500 mg are administered intravenously just before the incision. An epidural catheter may be placed if recommended by the anesthesiologist. A nasogastric tube is inserted.

#### Laparoscopic technique

The first port is inserted using open approach or by using an optic port. Subsequent ports are inserted under direct vision. The location of the ports is left to the surgeons discretion. The abdominal cavity is inspected and the caecum located and identified. Laparoscopic forceps are used to examine the small bowel starting from the terminal ileum until the transition site is identified. Dilated small bowel loops are not grasped, but can be mobilized by grasping the mesenterium. Once the transition site is identified, the obstructing adhesions are divided and the bowel is inspected for vitality. Ports are removed under vision, and possible bleeding is primarily controlled by ligatures. The fascial holes of ports over 5 mm are closed. A nasogastric tube is left in place.

#### Criteria for conversion to open surgery

– Confirmed or suspected small bowel perforation, which is not amenable for laparoscopic suturing

– A transition site is not identified

– The reason for obstruction is not found

– Peritoneal carcinosis is detected

– The presence of widespread diffuse adhesions

– Need for bowel resection - conversion can be made to minilaparotomy to exteriorize the small bowel section requiring resection

#### Open surgical technique

A midline incision is made and the abdominal cavity is inspected. The small bowel is examined until the transition site is located. Adhesions causing obstruction are divided. Excess fluid within small bowel are pushed into the stomach and the stomach is emptied using a nasogastric tube. The fascia is closed using continuous or interrupted sutures at surgeon’s discretion.

#### Postoperative treatment

The nasogastric tube is kept in place until the secretion is less than 500 ml per 8 hours. After the removal of the nasogastric tube, the patient can drink up to 200 ml per 6 hours. If no nausea develops, patient may drink freely. Proton pump inhibitors are used for the length of the hospital stay. Trombosis profylaxis is commenced 6 hours after surgery, if there is no suspicion of postoperative hemorrhage. Ibuprofen, paracetamol, tramadol, and oxycodone can be used for pain. Pain is evaluated using a visual analogue scale daily and before administering pain killers.

#### Criteria for discharge

– Passage of stool

– The patient tolerates per oral nutrition

– Sufficient pain relieve is achieved with ibuprofen, paracetamol, and/or tramadol.

#### Unresolving obstruction after surgery

If the obstruction if not resolved in spite of surgical treatment, the patient can undergo radiological imaging studies and/or surgical exploration (open or laparoscopic) at the discretion of the surgeon.

#### Surgeons

The same surgeons perform both open and laparoscopic operations. All participating surgeons must have solid experience and skills of complex laparoscopic procedures, and need to have perfomed at least two laparoscopic adhesiolysis for small bowel obstruction before operating on patients participating in the trial.

#### Follow-up

Patients of working age are given sick leave. The length of sick leave is at the discretion of treating physician, who is taking into consideration the patient’s age and type of work (physical or desk job). A follow-up call in scheduled within 30 days, and return to work, possible late complications and readmissions are registered. Follow-up questionnaires are sent 1, 5 and 10 years after the randomization, and in case of no response, patients are contacted by telephone. Information about possible hernias and recurrent bowel obstructions is solicited.

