### Secondary endpoints

– Passage of stool (post-operative days)

– Commencement of enteral nutrition (post-operative days)

– 30-day mortality

– Complications (all causes), graded by Clavien-Dindo classification

– Number of participants with iatrogenic small bowel lesions

– Number of participants with readmission(s)

– Number of participant with failure to resolve obstruction

– Pain scores on the Visual Analog Scale

– Length of epidural catheter analgesia (days)

– Total need of opioids in milligrams

– Length of sick leave (days)

– Conversion rate (laparoscopic group)

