### Data collection and analysis

Data will be collected by using an electronical case report form, and statistically analyzed in the main research center (Helsinki) once the trial is completed. Continuous variables will be compared using t-test or Mann–Whitney-U-test. Categorical variables will be compared using Fischer’s exact-test or Chi-square-test. Groups will be analyzed as intention-to-treat. An interim analysis will be made when 52 patients have been randomized and treated.

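### Sick leave is set with job type and age in mind, but the stated comparison ignores both and so gives up precision on this secondary endpoint

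*Protocol article*

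**What the plan says.** All references are to the protocol article.

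- **Secondary endpoints** lists "Length of sick leave (days"), eleventh of twelve, with no ranking among them.
- **Follow-up** limits who has the outcome: "Patients of working age are given sick leave". It also says who decides it: "The length of sick leave is at the discretion of treating physician", with "age and type of work (physical or desk job") as the considerations.
- **Exclusion criteria** rule out only "Age less than 18 years or over 95 years", so many enrolled patients may be past working age. Sick leave is therefore compared in a subset of the planned 102, whose size is not given.
- **Randomization procedure** describes 1:1 blocks "stratified by each study center". Age, employment and job type are not strata.
- **Data collection and analysis** gives one rule for all continuous outcomes: "Continuous variables will be compared using t-test or Mann–Whitney-U-test". No covariate is mentioned.

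**The concern.** The article itself names two determinants of this outcome that are fixed before randomisation. If physical workers are given longer leave than desk workers whichever operation they had, that difference adds to the spread within each arm. A plain two-sample test treats it as noise, although it could be accounted for.

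At stake is the width of the confidence interval, and hence the chance of detecting a real difference, for an endpoint that uses only part of the sample. Stratifying by centre does not balance job type or age in that subset, so neither the design nor the stated analysis uses this information.

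**Working it through.** **The plan's own figure.** The article states no figure for sick leave. Its only sample-size figure is for the primary endpoint, and it reproduces. The pooled SD is √((3.75² + 5²)/2) = 4.42 days. For a 2.5-day difference at two-sided 0.05 and 80% power, the t-test calculation gives 50.03, hence 51 per arm, or 102 in total. The sample size is not in question.

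**Inputs for sick leave, all assumed.** m = 25 working-age patients per arm (about half of 102); share in physical work p = 0.5; SD within job type s = 10 days; physical-minus-desk gap D = 3, 7, 14 or 21 days; true arm difference 7 days for the power column.

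**Formulas.**
- Variance between job types: B = D² × p(1 − p) = 0.25 D².
- Removable share of the variance: B / (B + s²).
- Unadjusted SE of the arm difference: √(s² + B) × √(2/m).
- Adjusted SE, approximately: s × √(2/m) = 10 × √0.08 = 2.83 days.
- Power: noncentral t, two-sided 0.05.

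| Gap D (days) | B | Removable share | SE unadjusted | SE adjusted | Power unadjusted | Power adjusted |
|---|---|---|---|---|---|---|
| 3 | 2.25 | 2% | 2.86 | 2.83 | 67% | 68% |
| 7 | 12.25 | 11% | 3.00 | 2.83 | 63% | 68% |
| 14 | 49 | 33% | 3.45 | 2.83 | 51% | 68% |
| 21 | 110.25 | 52% | 4.10 | 2.83 | 39% | 68% |

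For example, at D = 14 the removable share is 49/149 = 33%, and the unadjusted SE is √149 × √0.08 = 3.45.

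**Chance imbalance is the same quantity.** The shift in the arm difference caused by unequal shares of physical workers has SD D × √(2p(1 − p)/m): 1.0, 2.0 and 3.0 days for gaps of 7, 14 and 21 days. At D = 14 its variance is 196 × 0.02 = 3.92. Adding the adjusted variance, 2.83² = 8.00, gives 11.92 = 3.45², which is the unadjusted variance. The unadjusted SE therefore already contains the imbalance; it is not a further harm on top of lost precision.

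**Other assumptions.** The ratio of unadjusted to adjusted SE is √(1 + D² p(1 − p)/s²).
- Lowest, with p = 0.3, D = 7, s = 10: √(1 + 10.29/100) = 1.05.
- Highest, with p = 0.5, D = 14, s = 7: √(1 + 49/49) = 1.41.

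So for gaps of one to two weeks the unadjusted SE is about 5% to 41% larger.

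**Validity of the unadjusted test.** This was simulated with 52 patients, half in physical work, no arm effect and 10,000 runs per setting. The t-test rejected in 5.05% of runs (D = 14, s = 10) and 5.15% (D = 7, s = 7). With a true 5-day difference at D = 14, s = 10, power was 30% unadjusted and 42% adjusted for job type, which agrees with the formulas (31% and 43%).

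The contribution of age and the loss under the Mann–Whitney test were not quantified.

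**The case against.** The strongest reply is that nothing here is an error. An unadjusted comparison of randomised groups is valid, the analysis section is a short generic summary, and covariate adjustment of a secondary endpoint is ordinary material for an analysis plan that is not shown. The case report form is not shown either, so job type may already be recorded. Every input to the magnitude is assumed, and the article makes no power claim for sick leave.

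Most of this stands, and it limits the point to a suggestion about efficiency. It does not dispose of it: the article states a method for every continuous variable and, separately, states what drives this one. The remark is that the stated method fits the stated facts less well than a readily available alternative.

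Three stronger readings are tempting, and the document supports none of them.
- A reader might infer that the comparison is biased, with an excess of physical workers passing for a treatment effect. Randomisation makes such an excess a matter of chance, its variance is already in the standard error, and the type I error stays near 5%.
- A reader might infer that the result will be moved by days. That needs a job-type gap of about a week or more, which the article does not give. At a 3-day gap the 95% range is about 1.96 × 3 × √0.02 = ±0.8 days with 25 per arm.
- A reader might treat sick leave as one of the main secondary endpoints. The abstract mentions it, but the list is unranked.

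The objection also points to a separate weakness. The trial is open label and leave is discretionary, so knowledge of the arm could influence its length. Adjustment for job type and age would not remove that.

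**Conclusion.** The point holds as a minor one. The unadjusted test is valid but less precise than it need be, because job type and age, which the article names as determinants of sick leave, stay in the error term.

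The size is conditional. With 25 patients per arm, half in physical work and a within-job SD of 10 days, power for a 7-day difference would rise from 63%, 51% or 39% to 68% at gaps of 7, 14 or 21 days. At a 3-day gap the gain is about one percentage point. Which of these applies cannot be read from the article.

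Only one secondary endpoint is concerned. The primary endpoint and the 102 patients are unaffected.

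**What to change.** 1. Record employment status and job type (physical or desk) on the case report form before the randomisation envelope is opened, if this is not already done. Age is already needed for eligibility.
2. Define the analysis set for sick leave as patients employed at randomisation.
3. Pre-specify one adjusted comparison by intention to treat: either a linear model with arm, job type and age, or, if skewness is expected, a van Elteren test stratified by job type. Make the choice before any comparison by arm is seen.
4. Keep the unadjusted t-test or Mann–Whitney test as a sensitivity analysis.
5. Say in the report that leave was set by physicians in an open-label trial, since the adjustment does not address this.

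The cost is one extra field and a little more analysis, with no more patients. How physicians set leave does not change. For patients already enrolled, job type would have to be taken from records made before allocation, or reported as missing.

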### Primary endpoint

– Length of post-operative hospital stay (days)

### Secondary endpoints

– Passage of stool (post-operative days)

– Commencement of enteral nutrition (post-operative days)

– 30-day mortality

– Complications (all causes), graded by Clavien-Dindo classification

– Number of participants with iatrogenic small bowel lesions

– Number of participants with readmission(s)

– Number of participant with failure to resolve obstruction

– Pain scores on the Visual Analog Scale

– Length of epidural catheter analgesia (days)

– Total need of opioids in milligrams

– Length of sick leave (days)

– Conversion rate (laparoscopic group)

### Tertiary endpoints

– Number of participants who develop ventral hernia

– Number of patient with recurrent adhesive small bowel obstruction

### Data collection and analysis

Data will be collected by using an electronical case report form, and statistically analyzed in the main research center (Helsinki) once the trial is completed. Continuous variables will be compared using t-test or Mann–Whitney-U-test. Categorical variables will be compared using Fischer’s exact-test or Chi-square-test. Groups will be analyzed as intention-to-treat. An interim analysis will be made when 52 patients have been randomized and treated.

### Sample size calculation

Based on preliminary retrospective analysis on laparoscopic and open adhesiolysis we have estimated the standard deviation to be 3.75 days in laparoscopic group and 5 days in open surgery group. Sample size is calculated to be able to demostrate 2.5 day difference in the post-operative length of stay. 102 patients are needed to achieve 80% power with a significance level of 0.05.

### Registration

This trial has been registered at ClinicalTrials.gov (Identifier: NCT01867528).

## Discussion

While laparoscopy has become the treatment-of-choice in acute cholecystitis, acute appendicitis, and perforated peptic ulcer, there are still areas of emergency surgery that are under debate
[6,7]. It has been suggested that purulent peritonitis caused by acute diverticulitis can be treated by laparoscopic lavage
[8], and randomized studies are on their way to either prove or disprove this approach
[9,10].

As laparoscopic surgery is becoming more common in emergency surgery, adhesive SBO is the obvious next target for a laparoscopic approach
[1]. Although there are several retrospective series, and meta-analyses comparing open approach to laparoscopy, there are no prospective, randomized studies. A search for ongoing trials reveals that, except for this trial, there are no other prospective, randomized trials enrolling patients at the moment of writing. Although previous retrospective series have shown association of less complications and shorter hospital stay with the laparoscopic approach, all previous retrospective series are more or less biased as the easiest cases are selected for laparoscopic approach.

This trial aims to provide level Ib evidence for the use of laparoscopy in the treatment of adhesive SBO that is not resolving by conservative means. Two large meta-analyses have shown that the advancement of oral contrast agent (Gastrografin) to the colon predicts that the obstruction would resolve with 0.97 sensitivity and 0.96 speficity
[5,11]. Optimal timing of the abdominal radiograph to predict the success of nonoperative management is unknown
[5]. In this study, the sensitivity, specificity, positive and negative likelihood ratios for waiting 4–8 hours were similar to waiting 24 hours before abdominal radiograph is carried out
[5,11]. Thus, there appears to be no advantage of waiting more than 4–8 hours. In this trial, if the oral contrast agent is not detected in the colon after 8 hours the conservative management is considered a failure and operative management is warranted. Further, the intestine is decompressed using a nasogastric tube for a minimum of 12 hours before commencing the oral contrast agent study. Thus, in total, the nonoperative management trial takes at minimum 20 hours.

Because there are several exclusion criteria in this trial, the patients are selected, and the results will not be applicable to all patients presenting with an adhesive SBO. These exclusion criteria, however, should not be regarded as absolute contraindications for laparoscopic approach. Many of the exclusion criteria are relative contraindications (peritonitis, suspicion of other cause than adhesions, pregnancy, wide diffuse adhesions, peritoneal carcinosis) or predictors of failure of laparoscopic approach (endometriosis, earlier generalized peritonitis, over 3 open procedures, radiotherapy, vascular procedures)
[12]. Furthermore, earlier obesity surgery is an indication for laparoscopic approach, and these patients are excluded because we do not think it is ethical to randomize them for open approach. Some of the exclusion criteria (age >95 years, earlier abdominal surgery within 30 days, patient living in an institutional care, or prior hospital stay of over 1 week) were included to reduce the morbidity of the patients included in the study, as inclusion of a few of these patients in one of the arms would create a strong bias (i.e. the length of stay would be longer because of the morbidity of the patients, not because of the approach used).

The trial has been recruiting since summer 2013. Enrollment of the patients is estimated to last for 4–5 years and primary end-point results are estimated to be available in 2018.

## Abbreviations

SBO: Small bowel obstruction.
